## Abstract

**Background:**

Neuropsychological symptoms in the Cognitive, Energetic, Behavioural, and Affective (CEBA) domains are common in people with multiple sclerosis (PwMS) and can negatively affect societal participation. The current study aims to investigate whether there are combinations of symptoms in the different CEBA domains that consistently occur together, that is, if there are CEBA profiles that can be identified. If so, this study aims to develop a screening instrument identifying CEBA profiles in PwMS to select the most suitable neuropsychological rehabilitation treatment for a given CEBA profile and consequently improve the societal participation of PwMS.

**Methods:**

This study is an observational, prospective cohort study consisting of 3 phases. Phase 1 focuses on the identification of CEBA profiles in a large sample of PwMS (*n* = 300). Phase 2 focuses on validating these CEBA profiles through replication of results in a new sample (*n* = 100) and on the development of the screening instrument. Phase 3 focuses on qualitatively evaluating in a small group of PwMS whether the selected treatment is suitable for the given CEBA profile or whether existing neuropsychological treatments should be adapted to meet the needs of PwMS suffering from symptoms in multiple CEBA domains simultaneously. Primary outcome is the CEBA profile, which will be derived from performance on neuropsychological assessment consisting of tests and questionnaires regarding the CEBA domains using a latent profile analysis. Inclusion criteria include MS diagnosis, sufficient ability in the Dutch language, and an age between 18 and 70 years.

**Discussion:**

The results of the current study will contribute to a more comprehensive understanding of the entire spectrum of neuropsychological symptoms in PwMS. Identification of possible CEBA profiles, and accordingly, the development of a screening instrument determining the CEBA profile of PwMS in clinical practice, contributes to the timely referral of PwMS to the most suitable neuropsychological rehabilitation treatment. If necessary, adjustments to existing treatments will be suggested in order to sufficiently meet the needs of PwMS. All of this with the ultimate aim to improve societal participation, and thereby quality of life, of PwMS.

**Trial registration:**

Dutch Central Committee on Research Involving Human Subjects (CCMO) NL83954.042.23; ClinicalTrials.gov NCT06016309.

## Background

Multiple sclerosis (MS) is a disease of the central nervous system characterized by demyelination, inflammation, and neurodegeneration as its main underlying pathologic processes [1]. Approximately 2.8 million people are diagnosed with MS worldwide, and MS is the most common neurological disorder in young adults [2]. The widespread damage to the central nervous system has a variety of physical consequences, such as motor weakness, sensory disturbances and visual problems [3, 4]. In addition to these well-known physical consequences, neuropsychological symptoms are prevalent in MS as well, including cognitive impairments, lack of energy and fatigue, impaired social-behavioural functioning, and affective problems such as anxiety and depression [5–10]. MS usually starts in young adulthood, and at present, there is no cure for the disease [11], underlining the importance of providing people with MS (PwMS) with the best possible support in living with these symptoms.

Both the physical and neuropsychological symptoms of MS can negatively affect societal participation. Societal participation includes the engagement in life situations such as work, social relationships, and leisure activities, which are all crucial for well-being and quality of life [12–17]. To date, the focus in rehabilitation care for PwMS is primarily on physical treatment. Only few PwMS receive access to neuropsychological rehabilitation treatments, although several treatments targeting the neuropsychological symptoms that PwMS present with have been developed, with promising results for societal participation [18–21].

This gap in need for and access to neuropsychological rehabilitation treatment for PwMS could be due to various reasons. It is possible that medical practitioners who see PwMS for regular consultations lack awareness of and knowledge about neuropsychological symptoms and the existing treatments addressing these symptoms. In the already limited time that is usually available in such consultations [22], it is likely that there is a focus on the more visible physical symptoms by patients as well as practitioners [23]. Additionally, in some cases, neuropsychological assessment (NPA) might not occur due to the, by practitioners presumed, burden of undergoing such an assessment. As a consequence, the neuropsychological symptoms of PwMS may go unnoticed for an extended period of time, leaving PwMS to manage these symptoms on their own.

### Neuropsychological symptoms of MS

In the present study, we propose categorizing the neuropsychological symptoms of MS into the Cognitive, Energetic, Behavioural, and Affective (CEBA) domains.

Cognitive impairments are a core symptom of MS, with up to 70% of PwMS presenting with cognitive deficits. The most frequently affected cognitive functions include information processing speed, memory, attention and executive functioning [7, 9, 10]. With respect to the Energetic domain, fatigue is reported by up to 80% of PwMS, with 15–40% even reporting it to be their most debilitating symptom [8, 24–26]. Thus far, the terminology used to describe fatigue in MS varies from pathological fatigue [27] to cognitive fatigue [28] to fatigue in general [26, 29]. Definitions of these terms also vary: although some definitions underscore the different aspects of fatigue, by mentioning both physical and mental components [27], fatigue in MS often seems to be treated as a general concept. With physical as well as nonphysical components, both with different possible effects on societal participation and quality of life [8, 30]. Therefore, the mental and physical components of fatigue will be specifically included as separate constructs in the present study. Concerning the Behavioural domain, PwMS can present with impairments in social cognition [6, 31]. Social cognition involves a range of cognitive abilities that underlie the perception, understanding and reaction to social stimuli, thereby playing a crucial role in our behaviour when interacting with others. Social cognitive impairments frequently lead to behavioural changes which may negatively affect social relationships and social functioning [6, 32–34]. With regard to the Affective domain, PwMS present with higher depression rates than patients with most other chronic neurological diseases [35, 36], ranging from 14 to 54% [5, 37]. Symptoms of anxiety are also common, affecting 14 to 41% of PwMS [5].

Symptoms in all CEBA domains negatively affect social and occupational functioning and thereby societal participation in general, as well as quality of life, of PwMS [6–8, 32–34]. Considering the negative impact of symptoms in one single CEBA domain on societal participation, it seems likely that the co-occurrence of symptoms in multiple CEBA domains simultaneously might have an even greater negative effect on participation. However, this is unknown, since only univariate relationships between symptoms in the CEBA domains and restricted participation have been considered and established thus far [12–14, 16].

### Co-occurrence of symptoms in the different CEBA domains

Several studies have shown that in PwMS, symptoms in the different CEBA domains can occur simultaneously. Depression and anxiety, for example, have been linked to specific cognitive functions, with depression having a negative influence on multiple cognitive domains, including information processing speed, working memory, executive functioning, and attention [38–41], and anxiety primarily affecting information processing speed and nonverbal memory [41, 42]. In addition, depression is known to be related to fatigue [43, 44], and higher levels of self-reported anxiety and depression have been shown to be related to lower performance on tasks for social cognition [45]. Social cognition is correlated with traditional cognitive deficits as well, including attention, executive functioning and memory [6, 46]. Additionally, multiple studies [45, 47] have shown a relationship between social cognitive functioning and fatigue; that is, higher levels of psychosocial fatigue have been associated with inferior performance on tasks for social cognition.

Current neuropsychological rehabilitation treatments primarily focus on symptoms in one CEBA domain at a time. For instance, at present, there is a compensation strategy training targeting cognitive problems [20], a cognitive behavioural therapy focusing on reducing MS-related fatigue [18], a compensatory strategy training focusing on impairments in social cognition and social behaviour [21], and an acceptance and commitment therapy adapted to people with acquired brain injury, targeting anxiety and/or depressive symptoms [19]. Considering the aforementioned co-occurrence of symptoms in the different domains [41, 45], the question arises whether existing neuropsychological rehabilitation treatments sufficiently meet the needs of PwMS or whether these treatments need adaptation to provide appropriate care for PwMS suffering from symptoms in multiple CEBA domains simultaneously.

Up to now, to the best of our knowledge, it has not yet been investigated over the whole spectrum of CEBA domains whether certain combinations of affected domains commonly occur together. In other words, it is unknown whether there are certain CEBA profiles that typically occur among PwMS and, if so, how these combinations of symptoms affect societal participation. By extension, there is currently no standardized procedure for selecting the most suitable neuropsychological rehabilitation treatment for a given CEBA profile, and it is unknown whether the existing treatments adequately address the needs of PwMS with these CEBA profiles. Considering the aforementioned impact of neuropsychological symptoms on societal participation and quality of life, there is currently an unmet need in today’s care for PwMS.

### Objectives

The MS-CEBA study aims to identify possible different CEBA profiles and the relationships between such CEBA profiles and societal participation in PwMS. If different CEBA profiles can be established, the aim is to validate the CEBA profiles found in a new group of PwMS. If successful, our aim is to develop a compact neuropsychological screening instrument that is feasible for use in clinical practice and which allows the timely identification of specific CEBA profiles without putting an unnecessary load on PwMS. With this compact screening instrument, PwMS can be timely referred to the neuropsychological rehabilitation treatment most suitable for their specific CEBA profile. Subsequently, by means of a qualitative evaluation, it will be assessed whether this method of selecting treatment indeed proves effective and the selected treatment is suitable for the given CEBA profile or whether, in future research, the existing neuropsychological treatments should be adapted or combined to meet the needs of PwMS. All of this is done with the overarching aim to improve societal participation and quality of life of PwMS. These objectives and the associated subobjectives are presented in Table 1. The study will be divided into 3 phases, pertaining to [1] identification of the CEBA profiles, [2] validation of the profiles and development of the screening instrument, and [3] evaluation of the recommended neuropsychological rehabilitation treatment.

**Table 1 Tab1:** Objectives of the MS-CEBA study

***(1) Phase 1: To identify possible CEBA profiles among PwMS***	
To achieve this objective, it will be investigated (1a) which proportion of the PwMS present with which CEBA symptoms, (1b) if PwMS and healthy controls differ on scores on neuropsychological tests and questionnaires regarding the CEBA domains, and if so, on which domain(s) they differ, (1c) which CEBA profiles (i.e., clustering of CEBA symptoms) exist among PwMS, (1d) if CEBA symptoms of PwMS are stable over time, (1e) how the identified CEBA profiles relate with demographic and disease related characteristics, and (1f) to what extent societal participation of PwMS can be predicted by the identified CEBA profiles and/or CEBA symptoms	
***(2) Phase 2: To validate CEBA profiles and develop the CEBA screening instrument***	
To achieve these objectives, it will be investigated (2a) whether the identified CEBA profiles can be replicated in a new sample of PwMS. Subsequently, (2b) a feasible screening instrument allowing timely identification of CEBA profiles among PwMS will be developed, in order to indicate the most suitable neuropsychological rehabilitation treatment	
***(3) Phase 3: To evaluate the recommended neuropsychological rehabilitation treatment***	
To achieve this objective, it will be (3a) qualitatively evaluated in a small group of PwMS from Phase 2, who chose to enter neuropsychological rehabilitation treatment based on the advise of the screening instrument, whether the treatment was adequately matched to their expectations, and by extension it will be (3b) qualitatively evaluated whether adjustments to, or combining of existing neuropsychological rehabilitation treatment options for PwMS with a specific CEBA profile should be suggested for future research	

## Methods

### Study design

The MS-CEBA study is an observational, prospective, cohort study consisting of three phases, as outlined in Table 1. The study aims to include a group of 300 PwMS in Phase 1, of whom 54 will undergo retesting after one year to investigate the stability of the results. Additionally, a group of 100 healthy controls (HCs) will be included in Phase 1. After two years, a second group of 100 PwMS will be included in Phase 2 to investigate whether the results of Phase 1 can be replicated, thereby validating the CEBA profiles. A neuropsychological screening instrument for timely identification of CEBA profiles will then be developed. In Phase 3, a qualitative evaluation of a small group of PwMS (n = 10) from Phase 2 who sought neuropsychological rehabilitation treatment using the advice obtained with the screening instrument (as a part of clinical care, not an intervention in this study) will be performed to identify whether and how this treatment adequately matched their expectations. If necessary, suggestions for adjustments to, or combining of, existing neuropsychological treatments in future research will be made based on this evaluation.

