### Statistical analysis

For analysing the data, Statistical Package for the Social Sciences (SPSS) version 28.0 and/or R, possibly combined with Latent GOLD version 6.0 [50], depending on the availability of suitable packages in R, will be used. For all analyses, the nominal significance level will be set at α = 0.05, 2 sided. The numbering of the analyses described below corresponds to the numbering of the objectives displayed in Table 1*.* In the following, T0 refers to the first group of 300 PwMS, and T1 refers to the retesting of 54 PwMS.

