**Phase 1: Identification of possible CEBA profiles.** 1a) Summary statistics will be computed, describing percentages of PwMS (n = 300) with CEBA symptoms, based on scores on the neuropsychological tests and questionnaires regarding each CEBA domain; 1b) MANOVAs with follow-up ANOVAs will be computed comparing PwMS *(n* = 300) to HCs (*n* = 100) on scores on the neuropsychological tests and questionnaires regarding the Cognitive and Behavioural domain, and ANOVAs will be computed comparing PwMS to HCs on scores on questionnaires regarding the Energetic and Affective domain; for 1c) and 1e) a three-step mixture analysis will be computed [51]: step 1 is a latent profile analysis to identify clusters of PwMS with common CEBA profiles; step 2 is to estimate the posterior cluster membership probabilities of the model from step 1 for each PwMS in the sample, and step 3 is to relate the cluster membership probabilities from step 2 to relevant predictors, i.e., a regression analysis will be carried out to estimate the relationship between the CEBA profiles and the demographic and disease-related variables, with an adaptation to account for the fact that cluster membership is estimated, rather than observed; for 1d) repeated measures MANOVAs will be computed comparing T1 (n = 54) to T0 (n = 300) on the scores on neuropsychological tests and questionnaires for the Cognitive and Behavioural domain separately; if a time effect is indicated, these will be followed by post hoc analyses (repeated measures ANOVAs), to assess which variable(s) the time effect pertains to. A repeated measures ANOVA will be computed comparing T1 to T0 on the scores on questionnaires regarding the Energetic and Affective domain separately; 1f) regression analysis will be carried out, considering two competing models: model 1, using the membership of the CEBA profiles as a predictor; and model 2, using the most distinguishing outcome variables (scores on neuropsychological tests and questionnaires in each of the CEBA domains) as predictors.

**Phase 2: Validation of CEBA profiles and development of the CEBA screening instrument.** 2a) The posterior cluster membership probabilities of the selected latent profile model from Phase 1 will be estimated for each of the PwMS in the new sample (n = 100). The equality of the distributions of membership probabilities of the new sample and Phase 1 sample will be tested using a chi-square test. 

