### Sample size

The sample size calculations provided below were performed following *G*Power* [52]. Since for objective 2b and objectives 3a and 3b (Table 1), no statistical analyses will be carried out, a sample size calculation is not relevant for these objectives.

With regard to objectives 1a and 1c, here, the main study parameter is the CEBA profile, which is latent and thus needs to be derived from performance on neuropsychological tests and questionnaires regarding the CEBA domains. For identification of the CEBA profiles, latent profile analysis will be performed. A minimum sample size of 300 is suggested for latent profile analysis to ensure that there is sufficient power to estimate all model parameters and recover the true number of classes [53, 54]. Therefore, the aim is to include a minimum of 300 patients. For objective 1b, the main study parameters are possible differences between PwMS and HCs on neuropsychological tests and questionnaires regarding symptoms in the different CEBA domains, which will be investigated through the performance of MANOVAs and ANOVAs. A power calculation (with a medium effect size [Cohen’s f] = 0.5, α = 0.05, power = 0.95) results in a minimal sample size of n = 60, which is expected to be exceeded with our goal of including 300 PwMS and 100 HCs for comparison of performance in the CEBA domains. With regard to objective 1d, here, the main study parameters are possible differences in CEBA symptoms between T0 and T1, which are derived from scores on neuropsychological tests and questionnaires regarding the CEBA domains. To investigate the extent to which individual CEBA symptoms are stable over time, repeated measures MANOVAs and ANOVAs will be performed to compare T0 to T1. Within-between interactions will be used. Here, a power calculation using repeated measure analysis (with medium effect size Cohen’s f = 0.5, α = 0.05, and power = 0.95) results in a total sample size of n = 54. Therefore, the aim is to include a minimum of 54 patients for comparing T0 to T1. Since objectives 1e and 1f, as well as objective 2a, depend on the CEBA profiles yet to be identified, the corresponding analyses are considered exploratory, and therefore, no sample size calculation will be provided at this stage. At a later stage, after the CEBA profiles have been identified, sample size calculations for these objectives will be provided, again using *G*Power* [52].

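### Phase 2 validation rests on a chi-square test of equality with 100 new patients; a non-significant result cannot show that the profiles were replicated

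*Protocol article*

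**What the plan says.** Study design gives the purpose of the second sample: "a second group of 100 PwMS will be included in Phase 2", in order "to investigate whether the results of Phase 1 can be replicated, thereby validating the CEBA profiles". The screening instrument is developed after that, and the Objectives section makes its development conditional on successful validation.

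Statistical analysis, Phase 2, describes one analysis for objective 2a. It first carries the Phase 1 model over to the newcomers: "posterior cluster membership probabilities of the selected latent profile model from Phase 1 will be estimated for each of the PwMS". It then makes one comparison: "The equality of the distributions of membership probabilities of the new sample and Phase 1 sample will be tested using a chi-square test". For all analyses, "the nominal significance level will be set at α = 0.05, 2 sided". No statistical analysis is planned for objective 2b or Phase 3, so nothing else bears on validation.

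Sample size says of objectives 1e, 1f and 2a that "the corresponding analyses are considered exploratory, and therefore, no sample size calculation will be provided at this stage". It adds that "after the CEBA profiles have been identified, sample size calculations for these objectives will be provided". The figure of 100 is nevertheless already stated in the Abstract, Study design, Study procedures and Statistical analysis.

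**The concern.** Replication is a claim of sameness. The null hypothesis of the named test is that the two distributions are the same, so the test can yield evidence against replication but none for it. The result that suits the stated aim is failure to reject.

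Failure to reject also comes more easily with fewer patients or noisier measurement, so a weaker Phase 2 would be more likely to look like a successful one.

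What is at stake is the basis of the screening instrument and of the treatment advice attached to it. Both could go forward on profiles whose distribution had changed materially in the new sample.

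**Working it through.** The article gives no power, effect size or margin for 2a, so there is no figure to reproduce. The check asks what a non-significant result would rule out.

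**Inputs from the article.** Phase 1 n = 300 and Phase 2 n = 100 (Study design); two-sided alpha 0.05 and a chi-square test of equality (Statistical analysis).

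**Assumptions.** Four profiles unless stated; each patient counted in one profile without classification error; Pearson chi-square on the 2 × K table (K = number of profiles). One profile's share halves in Phase 2, and the lost share goes either equally to the other profiles or all to one of them.

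**Worked case: a 20% profile falls to 10%, loss spread, four profiles.**
- Phase 1 shares are 20% and three of 26.67%. Phase 2 shares are 10% and three of 30%.
- Pooled shares: 0.75 × 0.20 + 0.25 × 0.10 = 0.175, and 0.75 × 0.2667 + 0.25 × 0.30 = 0.275 for each of the others.
- Noncentrality: 300 × (0.025²/0.175 + 3 × 0.00833²/0.275) + 100 × (0.075²/0.175 + 3 × 0.025²/0.275) = 1.30 + 3.90 = 5.19.
- Against the critical value 7.81 (3 df), power is about 46%. Simulation gives 46% to 47%, so the change is missed 53% to 54% of the time.

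**Miss rate for a halved share, four profiles, by simulation (20,000 to 40,000 runs each).**

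| Phase 1 share | Loss spread over the others | One profile absorbs the loss |
|---|---|---|
| 10% | 81% | 77–78% |
| 15% | 68% | 60% |
| 20% | 53–54% | 41% |
| 25% | 39% | 24% |
| 30% | 26–27% | 13% |
| 40% | 10% | 2% |

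**Dependence on the number of profiles (loss spread, two to six profiles).** The miss rate runs from 35% to 62% at a share of 20%, from 12% to 35% at 30%, and from 3% to 16% at 40%.

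**Dependence on sample size.** With shares 40/20/20/20 becoming 50/20/20/10 and Phase 1 fixed at 300, the change is missed 72% of the time with 50 new patients, 47% with 100 and about 21% with 200. The fewer the patients, the more often the favourable result appears.

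**What 100 patients can support.** For a 20% profile, the standard error of the share difference is √(0.16/100 + 0.16/300) = 0.0462, and the 95% half-width is 1.96 × 0.0462 = 9.1 points. With no true difference, the power of two one-sided tests at 5% each is 2Φ(margin/SE − 1.645) − 1:
- 15-point margin: 2Φ(1.603) − 1 = 89%
- 10-point margin: 2Φ(0.520) − 1 = 40%

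Those tests correspond to a 90% interval inside the margin. If the full 95% interval must lie inside, replace 1.645 by 1.96: 2Φ(1.288) − 1 = 80% and 2Φ(0.205) − 1 = 16%. All these figures are for one profile. Requiring every profile to meet its margin lowers the power further.

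**The case against.** Four points can be made for the plan.

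- **The decision rule is not written down.** A reader might infer that the protocol declares p > 0.05 to be validation. It does not. It states an aim and names a test, and the link is implied because no other analysis serves that aim. A full protocol or analysis plan, not shown here, may hold a replication criterion. This stands as a limit on the wording. It does not remove the point, because the test and the conclusion that the article does name do not fit each other.
- **The analysis is labelled exploratory, and a sample-size calculation is promised.** Both are true and should be acknowledged. But a power calculation for a difference test leaves the inference pointing the same way, 100 is already stated, and an exploratory label sits uneasily with validation on which the instrument depends.
- **The loss of power is not general.** A reader might infer that any profile whose share halved would be missed half the time or more. The documents give neither the number of profiles nor their shares, and the table contradicts that reading for larger profiles.
- **Equivalence of shares is not replication of structure.** Shares could match while the profiles differ, or the profiles could re-emerge in a sample with a different case mix. This stands, and it limits what any test on shares can conclude.

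**Conclusion.** The point holds in this form: the named test cannot support the stated conclusion, because a non-significant result is not evidence of replication. This does not depend on any assumed figure.

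The size does depend on assumptions. With four profiles and error-free membership, the test at 300 versus 100 misses a halved share roughly 41% to 54% of the time for a 20% profile, 60% to 68% for a 15% profile and about 80% for a 10% profile. At 30% or more, the halving would usually be detected.

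Estimated membership would be expected to blur real differences and raise these rates. By how much cannot be worked out from the article, and no figure is claimed. The change is worth making before Phase 2 data are seen, but the rest of the plan does not depend on it.

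**What to change.** In Statistical analysis, Phase 2, objective 2a:

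1. State that p > 0.05 on the chi-square test will not be taken as replication.
2. Report each profile's Phase 2 minus Phase 1 share with a 95% confidence interval that allows for classification error.
3. Fix a margin after the Phase 1 profiles are known and before Phase 2 data are seen. Call the distribution replicated only if the intervals lie within it; otherwise call the result inconclusive. State the interval level used for this rule, since it changes the power as shown above.
4. Base the promised sample-size calculation for 2a on this margin, not on the difference test.
5. Limit the conclusion to the profile distribution, since matching shares alone do not show that the same profile structure re-emerges.

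The cost is analysis work and wording, with no extra patients. The article reports 167 participants so far and recruitment until the end of 2026, so there appears to be time. The downside is a weaker validation claim that may end as inconclusive, particularly with a margin near 10 points.
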